## Abstract

**OBJECTIVE::**

To describe the prespecified analysis plan for Protocolized Evaluation of Permissive Blood Pressure Targets vs. Usual Care (PRESSURE), a trial comparing a permissive mean arterial pressure (MAP) target above the age-specific fifth centile with usual care in critically ill children.

**DESIGN::**

Pragmatic, open, multicenter, parallel group randomized controlled trial with integrated economic evaluation.

**SETTING::**

Twenty-one PICUs in the United Kingdom.

**PATIENTS::**

Infants and children older than 38 weeks corrected gestational age to 16 years, accepted to a participating PICU, on invasive mechanical ventilation (IMV) and receiving vasoactive drugs for hypotension.

**INTERVENTION::**

Adjustment of hemodynamic support to achieve a permissive MAP target greater than the fifth centile for age during IMV.

**MEASUREMENTS AND MAIN RESULTS::**

The primary outcome is a composite 30-day mortality and duration of IMV, and it will be analyzed with a two-sample rank-sum test. Components will also be analyzed separately. Sensitivity analyses will adjust for adherence, and subgroup analyses will test interactions with baseline covariates. Secondary analyses will compare mortality at various time-points, duration of survival, time to liberation from IMV, functional status changes, receipt of renal replacement therapy and length of stay. The health economic analysis will follow the intention-to-treat principle and report the mean (95% CI) incremental costs, quality-adjusted life years and cost-effectiveness up to 12 months.

**CONCLUSIONS::**

Results will be reported following this plan through peer-reviewed publications and conference presentations.

RESEARCH IN CONTEXTThe previously published protocol article provides details on Protocolized Evaluation of Permissive Blood Pressure Targets vs. Usual Care (PRESSURE) trial rationale and delivery.This statistical analysis paper (SAP) describes the specific analysis strategies for testing the trial intervention.The SAP defines statistical and reporting procedures to ensure robust and unbiased evaluation of the trial objectives.

Hypotension (low blood pressure) is common among critically ill children. Interventions to treat hypotension include vasoactive drugs, IV fluids and central venous catheters. Although interventions are potentially lifesaving, there are also potential harms (1).

The Protocolized Evaluation of Permissive Blood Pressure Targets vs. Usual Care (PRESSURE) trial is a randomized controlled trial to evaluate the clinical and cost-effectiveness of permissive mean arterial pressure (MAP) target of greater than fifth centile for age compared with usual care. In this context, usual care is taken to mean blood pressure management without a protocolized MAP target, reflecting real-world practice in U.K. PICU.

PRESSURE is testing the hypothesis that the benefits of reduced exposure to hypotension treatments outweigh the risks of lower blood pressure. Further details of trial rationale and delivery can be found in the PRESSURE protocol article (2).

This article describes the proposed statistical and health economics analyses plan for the PRESSURE trial in accordance with published guidelines (3).

## METHODS

### Trial Design and Randomization

PRESSURE is a pragmatic, multicenter, parallel group, superiority randomized controlled trial. Eligible patients are randomized to either usual care or the permissive MAP target arm (age-dependent target). Allocation is by randomized permuted blocks with variable block lengths, stratified by site and age category (younger than 12 mo; 1 yr to younger than 3 yr; 3 yr or older).

### Sample Size

The sample size calculation used observational data from the Permissive vs. Restrictive Temperature Thresholds in Critically Ill Children with Fever and Infection (FEVER) study (4) which included 22 of 28 PICU wider National Health Service (NHS) units (*n* = 4126) and 6 months of eligible admissions.

Power estimates used 10,000 simulated trial datasets with distributions of mortality (13%) and duration of invasive mechanical ventilation (IMV) (log-normal distribution with mean = 7.8, sd = 9.5 d). To achieve 90% power, 1900 participants are required to detect a clinically meaningful mortality reduction of 2% (13–11%), and an 18-hour reduction in mean ventilator duration (7.8–7.1 d) in survivors, allowing for 10% withdrawal/refusal of deferred consent.

### Statistical Interim Analyses and Stopping Guidance

The internal pilot phase will be evaluated 6 months after the trial opens to recruitment against prespecified criteria (site opening, recruitment rate, and separation between groups in mean MAP and duration of vasoactives). A single-interim analysis will be carried out after recruitment 30-day follow-up of 950 patients. The composite primary endpoint will be analyzed in the intention-to-treat (ITT) population using a two-sample Wilcoxon rank-sum (Mann-Whitney) test, with early termination recommended if any one arm is shown to be superior with *p* value of less than 0.001 (Peto-Haybittle stopping rule).

### Timing of Final Analysis

The main analysis of the trial will be conducted after all patients randomized to the trial have completed 90-day follow-up, with one further update after 12-month follow-up.

### Research Ethics

The PRESSURE trial and consent procedures were approved by the East of United Kingdom–Cambridge South Research Ethics Committee (21/EE/0084; IRAS 289545) on May 10, 2021. The trial is registered with an International Standard Randomized Controlled Trial Number (20609635), and all procedures comply with the approved protocol and the Helsinki Declaration (1975, and later amendments).

## STATISTICAL PRINCIPLES

### CIs and *p* Values

The primary clinical endpoint will be tested for superiority. Secondary outcomes will be tested where specified or summarized descriptively. All tests will be two-sided with significance at *p* value of less than 0.05, and effect estimates presented with 95% CIs. No adjustments will be made for multiple testing.

### Adherence and Protocol Deviations

Exposure will be assessed and reported for each treatment group using: highest and mean MAP (recorded hourly until discontinuation of vasoactive agents for ≥ 24 hr or at PICU discharge); vasoactive receipt and duration to the end of first episode (defined as no vasoactive agents received for≥ 24 hr); dose-rate, total dose, total days on vasoactive agent at PICU discharge, number of treatment episodes; fluid balance; and urine output.

Vasoactive agent receipt will be summarized as number (%) of patients receiving each drug; other parameters will be reported as mean (sd) or median (interquartile range [IQR]), as appropriate. Norepinephrine equivalence will be calculated as previously described (5) (**Table 1**). Data on vasoactive drugs not included in the norepinephrine equivalence formula (e.g., milrinone) will be presented separately. Vasoactive agent infusions are recorded hourly and assumed to last one hour for total dose calculations.

**TABLE 1. T1:** Conversion Method for Calculating Norepinephrine Equivalents (5)

Vasopressor	Unit	Conversion Factor for Norepinephrine Equivalent
Norepinephrine	μg kg^−1^ min^−1^	× 1
Epinephrine	μg kg^−1^ min^−1^	× 1
Dopamine	μg kg^−1^ min^−1^	/150
Phenylephrine	μg kg^−1^ min^−1^	× 0.1
Vasopressin	U min^−1^	× 2.5

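### Table 1 combines vasopressin in absolute units per minute with four drugs dosed per kilogram, so the norepinephrine-equivalent dose is not comparable across body weights (a descriptive exposure measure only)

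*SAP article*

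**What the plan says.** Under Adherence and Protocol Deviations, the SAP article lists the exposure measures to be reported for each arm. They include "dose-rate, total dose, total days on vasoactive agent at PICU discharge, number of treatment episodes". The same section states that "Norepinephrine equivalence will be calculated as previously described (5") and gives the conversion in Table 1. Four drugs in that table have the unit μg/kg/min: norepinephrine (× 1), epinephrine (× 1), dopamine (/150) and phenylephrine (× 0.1). The fifth row reads "Vasopressin U min^−1^ × 2.5", with no kilogram in the unit.

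Drugs outside the table are kept apart: "Data on vasoactive drugs not included in the norepinephrine equivalence formula (e.g., milrinone) will be presented separately". Vasopressin is in the table, so it falls inside the formula. Separately from dose, "Vasoactive agent receipt will be summarized as number (%) of patients receiving each drug".

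The Abstract gives the population as "Infants and children older than 38 weeks corrected gestational age to 16 years". Under Trial Design and Randomization, allocation is "stratified by site and age category (younger than 12 mo; 1 yr to younger than 3 yr; 3 yr or older"), so children under one year form a stratum of their own.

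Nothing in the article converts vasopressin to a per-kilogram rate, rescales the factor for children or comments on the difference in units.

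**The concern.** An equivalence formula is meant to put several drugs on one scale so that they can be added. Here four terms are already divided by body weight and one is not. In a population with a narrow weight range, a fixed factor can absorb the difference. From term infants to 16-year-olds it cannot, because the same number on the equivalent scale stands for different per-kilogram vasopressin exposure in different children.

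The trial's hypothesis is that less exposure to treatments for hypotension brings more benefit than lower pressure brings harm, so a reader will want to see how far exposure differed between arms. Dose-rate and total dose are part of that account, and the norepinephrine equivalent is the only stated means of combining drugs into one dose. If vasopressin is under-weighted in the smallest children, that part of the account is incomplete for them, and dose summaries cannot be compared across age groups.

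**Working it through.** The plan gives no figure that can be reproduced here. The check is one of units, followed by arithmetic on assumed weights.

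**Inputs from the SAP article**
- Vasopressin: U/min, factor 2.5 (Table 1).
- Other four drugs: μg/kg/min, with the factors in Table 1.
- Hourly infusion records, each taken to last one hour when total dose is calculated (Adherence and Protocol Deviations).

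**Assumptions not in the article (for arithmetic only)**
- Body weights of 3.5 to 70 kg.
- Reference weights of 50 to 80 kg.
- Vasopressin given at a rate that scales with weight.
- The equivalents of the separate drugs are summed. The article does not write out the sum, but a single formula with one output scale implies it.

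**Step 1: dependence on weight.** Let *d* be the vasopressin rate in U/kg/min and *W* the weight in kg. The absolute rate is *d* × *W*, so

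vasopressin term = 2.5 × *d* × *W*.

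At a fixed *d* this is proportional to *W*. The other four terms do not change with *W* once the rate is in μg/kg/min.

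**Step 2: relative size.** At equal *d*, the term relative to its value at a reference weight is *W* / *W*ref, whatever *d* is.

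| Weight | Relative to 70 kg | Range for *W*ref = 80 to 50 kg |
|---|---|---|
| 3.5 kg | 3.5/70 = 5.0% | 4.4% to 7.0% |
| 5 kg | 5/70 = 7.1% | 6.25% to 10.0% |
| 10 kg | 10/70 = 14.3% | 12.5% to 20.0% |
| 30 kg | 30/70 = 42.9% | 37.5% to 60.0% |

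**Step 3: effect on the sum.** Purely to illustrate, take *d* = 0.0005 U/kg/min alongside norepinephrine at 0.1 μg/kg/min.

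- 5 kg: term = 2.5 × 0.0005 × 5 = 0.00625; share = 0.00625 / 0.10625 = 5.9%.
- 10 kg: term = 0.0125; share = 0.0125 / 0.1125 = 11.1%.
- 70 kg: term = 0.0875; share = 0.0875 / 0.1875 = 46.7%.

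Per-kilogram exposure to both drugs is the same in all three patients. These shares depend on the two assumed rates; the ratios in Step 2 do not.

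**Step 4: total dose.** Total dose adds hourly rates, each held for one hour. For a given child the factor *W* is common to every hour, so the ratios in Step 2 carry over unchanged.

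**Step 5: the opposite assumption.** Suppose the absolute rate in U/min were the same at every weight. The term would then not shrink in infants. But a 5 kg infant would have 70/5 = 14 times the per-kilogram exposure of a 70 kg adolescent and receive the same equivalent. The direction of the distortion depends on how the drug is given. The lack of comparability does not.

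**Step 6: where the measure is used.** Norepinephrine equivalence does not enter the primary or secondary outcomes or their analyses. It plays no part in the deviation rule under Protocol Adherence, which concerns MAP above range for three hours without stopping or lowering the infusion. Nor does it enter the complier average causal effect analysis under Sensitivity Analyses. It is summarised by mean (SD) or median (IQR), and no test is specified.

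**The case against.** The strongest reply is that little depends on this measure. Under Statistical Interim Analyses and Stopping Guidance, the pilot's separation criteria are mean MAP and duration of vasoactives; dose is not among them. Vasopressin use by arm can be seen from the count of patients receiving each drug. Duration, total days and number of episodes need no conversion. The weight scaling is the same in both arms, and stratification by age should keep weights similar between them, so a spurious difference between arms is not to be expected. All of this stands, and it limits the point to a descriptive summary.

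A reader might infer that vasopressin exposure in infants all but disappears from the trial's results, or that a difference between arms in small children would go unseen. The article does not support either. The first needs weight-scaled administration, which is not stated, and concerns only the combined dose. The second overlooks the reporting of receipt and duration. What could be missed is narrower: a difference in vasopressin dose among small children that neither receipt nor duration reflects. Nor does the article make dose the means by which separation is demonstrated; it is one exposure measure among several.

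It can also be said that the formula is taken from a cited source, and that this source or a fuller plan may deal with children. Neither can be checked here. A citation does not make a fixed factor independent of weight, and Table 1 as printed contains the mismatch.

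**Conclusion.** The point holds as a minor inconsistency of units. Table 1 mixes one absolute rate with four per-kilogram rates, and a fixed factor of 2.5 cannot be right across the trial's age range. That conclusion needs only the summation implied by the formula.

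The size and direction rest on the assumption that vasopressin rates scale with weight. Under it, the contribution is about 7% at 5 kg and 14% at 10 kg of that at an assumed 70 kg. With reference weights of 50 to 80 kg the ranges are 6.25% to 10% and 12.5% to 20%. The summed dose-rate and total dose would then under-count vasopressin in small children.

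The consequence is a blurred description of how far the arms differed in vasoactive dose, and dose summaries that cannot be compared across ages. No efficacy result, deviation count or adherence-adjusted estimate is affected.

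**What to change.** Take vasopressin out of the summed norepinephrine equivalent. Present its weight-indexed dose-rate and total dose separately by arm, as the plan already does for milrinone. This needs no new conversion factor.

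If the sponsor prefers to keep vasopressin in the sum, Table 1 should use a weight-indexed conversion with a stated justification, and a sensitivity summary should exclude vasopressin. Rescaling 2.5 by a reference weight is not self-evident: the factor per U/kg/min would be 2.5 × 50 = 125, 2.5 × 70 = 175 or 2.5 × 80 = 200, depending on the weight assumed, and the article offers no basis for choosing.

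The cost is one row of Table 1, a sentence of text and a line of code. Body weight is needed for each child who received vasopressin. If the drug is charted per kilogram, Table 1 as printed needs the weight as well. The one small drawback is that the departure from the cited formula must be stated. The change concerns the analysis conversion only and has no bearing on how any drug is given.

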### Protocol Adherence

The number (%) of patients deemed ineligible after randomization will be reported by treatment group, along with reasons for ineligibility.

Failure to discontinue vasoactive agents or reduce dose-rate once MAP is above the upper limit of the age-specific MAP target range for at least three consecutive hours in the permissive MAP target group defines a potential protocol deviation. Potential deviations will be adjudicated and may be deemed as an “acceptable” reason (**Table 2**), and the total number will be reported. Full adherence is defined as no “unacceptable deviations.” For each patient in the permissive MAP target group, the following adherence measures will be calculated: total time on vasoactive agents with MAP 1) within range, 2) above range, 3) greater than 5 mm Hg above the upper limit, and 4) below range, and summarized descriptively.

**TABLE 2. T2:** Deviation Categories Following Adjudication Procedure

Unacceptable reasons
Deviation—clinician decision
Deviation—staffing issues/awareness
Unknown/not documented
Acceptable reasons
Patient developed an exclusion criterion postrandomization
Attempt to deliver protocol—volatile mean arterial pressure
Attempt to deliver protocol—monitoring issue
Patient met exclusion criteria at time of randomization
On vasoactives for an indication other than hypotension
Patient met an exclusion criterion at the time of randomization
Protocol not followed while outside of ICU

Categories may change before the final analysis.

### Analysis Population

Following the ITT principle, all randomized patients will be included in the primary analysis, excluding patients that have requested removal of all data. Analysis of secondary outcomes will additionally exclude those where consent to access medical records was withheld or unobtainable before the outcome timepoint.

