### Consent

The parent or legal guardian will be asked to provide consent as soon as appropriate after randomization. This model of consent, research without prior consent or “deferred consent” is increasingly used emergency care trials in many jurisdictions (7). Once given, consent can be withdrawn at any time.

If access to medical records is declined, data collection and any linkage to national datasets will not occur. Unless removal is explicitly requested, data collected up to refusal or withdrawal will be retained, and a minimal dataset including primary outcome data will be collected. If trial continuation is refused but access to medical records is granted, data collection and linkage will continue, and the patient may be included in the analysis as appropriate.

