## ANALYSIS

### Outcome Definitions

#### Primary Clinical Outcome

The primary outcome is a composite of death and duration of IMV at 30 days postrandomization. Patients who die on or before day 30 are assigned the worst score of 31. Surviving patients are scored by the total calendar days on IMV from day 1 (randomization) to day 30, including any IMV during readmissions to PICU.

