### Clinical Effectiveness Analysis Methods

#### Primary Outcome

The primary clinical outcome will be summarized by arm (median, IQR, graphically) and analyzed using a two-sample rank-sum (Wilcoxon-Mann-Whitney) test (10). The primary effect estimate will be the probabilistic index, the probability that intervention is superior to control for the composite outcome, and 95% CI. The separate components will also be presented by arm with effect sizes and 95% CIs, following established guidelines (11). Mortality will be analyzed using logistic regression, adjusting for age (younger than1 yr; 1 yr to younger than 3 yr; 3 yr or older), and site as a random effect. Duration of IMV will be analyzed using a two-sample rank-sum test.

Ordered logistic regression will estimate the proportional odds ratio, adjusting for baseline variables. The unadjusted OR will be presented for comparison. If data completeness allows, the following variables will be used in adjusted analyses: predicted log odds of mortality at randomization (Paediatric Index of Mortality, version 3 [PIM-3] score (12) [continuous; linear]); primary reason for admission (suspected/proven infection vs. other); comorbidities (neurologic vs. non-neurologic vs. none); age (continuous; restricted cubic splines with four knots at the 5th, 35th, 65th, and 95th percentiles); and site (random effect).

Baseline covariates were prespecified based on anticipated associations with the outcomes. Results will be reported as adjusted odds ratios with 95% CI.

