#### Secondary Outcomes

Mortality outcomes will be compared using Fisher exact test. If suitable, logistic regression will be used, adjusted for baseline variables.

Duration of survival will be plotted as Kaplan-Meier survival curves by arm. An adjusted hazard ratio will be calculated using Cox proportional hazards regression.

Time to liberation from IMV will be reported as median time (with 95% CI) by arm using Kaplan-Meier methods. An adjusted hazard ratio will be calculated using Cox proportional hazards regression.

Change in functional status will be analyzed using adjusted linear regression, additionally adjusting for baseline status. Receipt of RRT at 30 days will be reported as median and IQR for patients surviving to day 30 and compared between groups using a Wilcoxon rank-sum test. Length of PICU and acute hospital stay will be compared using a Wilcoxon rank-sum test and reported by group using medians and IQRs in patients stratified by survival status. HrQoL score for survivors (12 mo) will be reported and a linear regression model adjusting for baseline variables will be applied to report incremental effect.

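### The consent-based exclusion also applies to 30-day mortality, which the trial already holds for the same children, so that outcome gets two populations and differing analyses

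*SAP article*

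**What the plan says.** Under Analysis Population, the primary analysis follows intention to treat: "all randomized patients will be included in the primary analysis, excluding patients that have requested removal of all data". The next sentence narrows the set for everything else: "Analysis of secondary outcomes will additionally exclude those where consent to access medical records was withheld or unobtainable before the outcome timepoint". It makes no exception for mortality. Table 3 lists mortality at PICU discharge, 30 days, 90 days and 12 months, and duration of survival, among the secondary outcomes.

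The Consent section describes deferred consent: "The parent or legal guardian will be asked to provide consent as soon as appropriate after randomization". If record access is declined, general data collection and linkage stop. Unless removal is requested, however, "data collected up to refusal or withdrawal will be retained, and a minimal dataset including primary outcome data will be collected". Under Primary Clinical Outcome, "Patients who die on or before day 30 are assigned the worst score of 31", so the primary outcome cannot be scored without knowing whether the child died by day 30.

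Two sections then analyse 30-day death. As a component of the primary outcome: "Mortality will be analyzed using logistic regression, adjusting for age" category, with site as a random effect. As a secondary outcome: "Mortality outcomes will be compared using Fisher exact test", followed by logistic regression adjusted for baseline variables if that is suitable.

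**The concern.** An exclusion decided after randomization can depend on what happened to the child. Consent is sought later, the allocation is open, and a child who dies early leaves less time for consent to be obtained. If deaths are over-represented among those without consent, the analysed mortality is too low in both arms. If the number or mix of such children also differs between arms, the comparison itself is biased.

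For outcomes that need records after a refusal, some loss is unavoidable. For 30-day mortality it is not, because the same death is counted in the primary analysis and omitted from the secondary one. Mortality is also the outcome that readers will look to first when judging the safety of a lower blood-pressure target.

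The second difficulty needs no assumption about consent. One quantity, 30-day mortality, will be reported from two sets of children and by different methods, and nothing says which is the trial's result.

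**Working it through.** **1. The plan's own figures.** Sample Size gives 13% v 11% mortality, mean ventilation 7.8 v 7.1 days (SD 9.5), 90% power, 1900 children and a 10% allowance. The allowance checks: 1900 × 0.90 = 1710, or 855 per arm. Simulating 10,000 trials with the rank-sum test at 855 per arm, deaths scored 31 and the SD held at 9.5 in both arms, gave power of 0.88 for a treated mean of 7.1 days and 0.91 for 7.05 days (exactly 18 hours). This brackets the stated 90%. (Holding the coefficient of variation constant instead gives 0.61 to 0.66.) These figures concern the primary test. The plan gives no figure for the share excluded under the consent rule or for mortality in that group.

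**2. The passages side by side, for a child whose record access is refused but whose data are not removed.**
- Primary analysis: included (Analysis Population).
- Day-30 vital status: collected (Consent, minimal dataset) and needed for the score (Primary Clinical Outcome).
- Mortality as a component: included, reading the component analysis as part of the primary analysis; mixed logistic regression with age category and site.
- 30-day mortality as a secondary outcome: excluded; Fisher exact test, and adjusted logistic regression if suitable.

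For a child whose consent was unobtainable rather than refused, the minimal-dataset sentence is not explicit. Analysis Population still places that child in the primary analysis, so day-30 status is needed there too.

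**3. False difference with no true effect.** Let f be the fraction excluded and m the mortality among the excluded. With true mortality 13% in both arms,

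analysed mortality = (0.13 − f·m) / (1 − f).

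The values of f and m are assumptions.
- m = 0.13 (exclusion unrelated to death): 13.0% for any f, so no difference.
- m = 0.25: f = 0.08 gives 0.110/0.92 = 11.96%; f = 0.12 gives 0.100/0.88 = 11.36%. Difference 0.6 points.
- m = 0.40: f = 0.08 gives 0.098/0.92 = 10.65%; f = 0.12 gives 0.082/0.88 = 9.32%. Difference 1.3 points.
- A more extreme imbalance, f = 0.05 v 0.15: 12.37% v 10.88% at m = 0.25 (1.5 points) and 11.58% v 8.24% at m = 0.40 (3.3 points).
- Equal f and equal m in both arms: no false difference, although the level falls. At f = 0.10 it is 0.105/0.90 = 11.7% for m = 0.25 and 0.090/0.90 = 10.0% for m = 0.40.

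**4. Same mechanism in both arms, true 13% v 11%.** Suppose 10% of control children are excluded and 30% of those are deaths. Then 0.10 × 0.30/0.13 = 23.1% of deaths and 0.10 × 0.70/0.87 = 8.0% of survivors are lost. Applying these rates to both arms gives 11.1% v 9.4%, so the 2.0-point difference shrinks to 1.7. If 5% are excluded and 30% of those are deaths, it is 12.1% v 10.2%, or 1.9 points.

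**The case against.** A reader might infer that the rule does remove early deaths, on the view that a child who dies before the family is approached is the usual case of unobtainable consent. The document does not say this. Unobtainable is not the same as not yet obtained, families can be approached after a death, and procedures for bereaved families are commonly left to the protocol. What stands is narrower: the SAP article does not say how deaths before consent are classified, so selective loss is possible.

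A reader might also set the fall from 13% to 11.7% or 10.0% beside the 2-point target. That is the wrong comparison. The first of these is only 1.3 points, and both are shifts in level common to the two arms, not treatment differences. Nor is the 10% allowance a rate for this rule. It covers withdrawal and refusal of deferred consent, and families who refuse continuation but grant record access stay in data collection, so the excluded share could be smaller.

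On the two analyses, the other side can fairly say that both sections foresee logistic regression, that reporting the components of a composite is customary, and that an unadjusted test beside an adjusted model is ordinary. This weakens any complaint about Fisher's test as such. It does not remove the difference in population or the lack of a rule for which result is the main one.

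Finally, respecting a refusal is a sound reason to exclude a child from record-dependent outcomes. It does not reach 30-day death, which is already collected and analysed. The planned flow diagram would show an imbalance in data availability but would not correct it.

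**Conclusion.** The inconsistency is in the text: the consent exclusion covers 30-day mortality although the primary analysis holds and uses that status for the same children. Followed as written, it drops known outcomes after randomization in an open trial, and it yields more than one 30-day mortality result without ranking them.

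The size of any bias is unknown. The 0.6 to 1.3 points rest on assumed exclusion of 8% v 12% and assumed mortality of 25% to 40% among the excluded; the larger figures need a 5% v 15% imbalance. If exclusion is unrelated to death, the bias is nil.

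Severity is moderate. The rank-sum test, the probabilistic index and the stated sample size are unaffected. Mortality alone was never well powered: 13% v 11% has about 25% power at 855 per arm and 27% at 950.

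**What to change.** 1. Exempt 30-day mortality from the consent exclusion. Analyse it in the primary population, leaving out only those who requested removal of all data, and state that children who die before consent is sought are included.
2. Treat any death already retained at the time of refusal in the same way for the other mortality outcomes. Where later status is unknown because access was refused, report it as missing by arm, so that retained deaths are not counted against a silently reduced denominator.
3. Name the mixed logistic model in the Primary Outcome section (age category, site) as the single main result for 30-day mortality. Any other analysis of it is supportive.
4. For duration of survival, include each child up to the last date on which vital status is lawfully held and censor there.
5. Keep the exclusion for outcomes that need records after a refusal.

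For 30-day mortality this is a change of wording and needs no new data. Beyond day 30 the gain is limited, because the minimal dataset is assured only for primary outcome data. The price is slightly different denominators across secondary outcomes, and censoring at refusal that may itself be informative and should be acknowledged as such.
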